### Randomisation and treatment allocation concealment

A block randomisation method will be used to randomise subjects into groups that result in equal sample sizes. This method will ensure a balance in sample size across both groups over time. Blocks are small and balanced with pre-determined group assignments, which keeps the numbers of subjects in each group similar at all times, whilst ensuring there is a 50:50 likelihood of participants being allocated to either group. Due to the possible influence of gender on the efficacy of strengthening exercise [32, 33], the study will only recruit male participants. After patient eligibility has been confirmed and informed consent obtained, a sealed envelope will be opened to reveal group allocation by an independent administrator not involved in the recruitment, treatment or assessment of study outcomes. A plain language statement will inform participants that they have an equal chance of receiving the residential MDT or individualised outpatient intervention. Group allocation will be documented and communicated to the supervising therapists by the independent administrator. Prior to the study, all treating staff will have received a briefing on the study protocol, the ethical, clinical and scientific basis of the study, the randomisation process and specific intervention for each treatment group, in line with the study protocol. It is not possible, relevant or necessary to blind participants to treatment allocation in this study. The clinical staff supervising both groups will be, by necessity, unblinded. Day and Altman [34] suggest blinding assessment by using non-involved assessors to record outcome scores. This is not possible in our study as independent assessors with specific knowledge of quantification of clinical outcomes are not available due to specialist staff man-power limitations. To minimise the potential influence of outcome assessors, instructions are standardised to ensure consistency in measurement. A medical statistician assisting with statistical analysis will be blind to group allocation until completion of the analysis.

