***The Visual Analogue Pain Scale***
*.* A visual analogue scale (VAS) will be used to measure pain intensity. The patient will be asked to rate their worst hip/groin pain experienced over the past 24-h using a 100 mm horizontal VAS anchored by the terms ‘no pain’ and ‘worst pain possible’. The supervising physiotherapist will also enquire if the sensation of pain is sharp or a dull ache, and if pain is made worse by movement. The 100-point VAS scoring requires no mathematical transformation, and with a normal distribution of data, it allows for parametric statistical analysis [60]. The VAS response format has shown good internal consistency, is easy to understand, is in wide clinical use, and has been sufficiently evaluated in clinical trials [60, 61].

The secondary outcome measures and instruments will be:
***EuroQuol-5D(EQ-5D-3L)***. The EQ-5D is a standardised, validated questionnaire for the self-rating of a patient’s health status [62]. It comprises a visual analogue scale (VAS) measuring self-rated health and a health status instrument consisting of a three-level response (no problems, some problems and extreme problems) for five domains [63]; (a) mobility, (b) self-care, (c) usual activities, (d) pain and discomfort and (anxiety and depression). A respondents EQ-VAS gives self-rated health on a scale where the endpoints are labelled ‘best imaginable health state’ (100) and ‘worst imaginable health’ (0). The EQ-5D has been shown to provide more exact ratings of everyday activities and their disease-related restrictions compared with other measures of health related quality of life (QOL) [64]. The inherent consistency of the EQ-5D test has been evaluated in the literature and shown good responsiveness to change in patients with hip conditions [65], and has been used in similar populations with similar musculoskeletal complaints to our study population [66].

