^2^ test. A significance level of 0.05 will be set for any inferential statistics conducted. The inclusion of the post treatment (T2) measure may help reveal if any differences occur as a consequence of the different interventions (as T2 reflects the immediate post-treatment scores for each group). However, this is based on the assumption that any changes in outcome from T1 and T2 (over 1 and 6-weeks) are linear, and also between T2 and T3. We recognise if the trend is non-linear then we will have insufficient data points to model the outcome over time in a way that will enable us to compare the trajectory of patient outcomes using the 3 time points. If interim analysis reveals this to be the case, we will remove T2 measures from the final analysis.

Secondary analysis will be undertaken to assess the predictors of outcome at the primary endpoint (12 weeks post treatment commencement) in both groups, using multiple regression analysis. Predictor variables including age, gender, baseline pain, physical function, duration of symptoms, mood/anxiety, self-efficacy, co-morbidities and exercise adherence will be measured. Analyses will be performed separately for MDT and IP group treatments. Response variables will be change in HAGOS function in daily living score pre and post intervention (MCID > 5.2 points) and numeric pain rating on the VAS. All predictors will be checked for collinearity. Univariate logistic regression will be performed on all potential predictors and those associated with the outcomes will be entered into the multivariate logistic regression model. Variables with the lowest predictive value will be removed from the model if *p* > 0.05. Odds ratios and 95 % CI’s will be calculated for all final predictors.

No statistical adjustment will be made for multiple testing. All tests will be two-sided and carried out at the 5 % level of significance. Changes to the study design or analysis plan will be documented with full justification. A statistician will oversee the blinded analyses of the data. The statistical analysis procedure will be discussed, reviewed and co-worked with statisticians at the Department for Health University of Bath, and School of Clinical Sciences at Bristol University.

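### The secondary predictor analysis is inconsistently specified (no VAS cut-off for a logistic model, gender as a predictor in an all-male trial), and its arm-by-arm p-value selection leaves at most about 2.7 events per usable candidate predictor at the expected dropout

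*Protocol article*

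**What the plan says.** The Statistical analysis section of the protocol article sets out a secondary analysis to "assess the predictors of outcome at the primary endpoint". The same sentence places that endpoint 12 weeks after treatment starts, and names multiple regression in both groups.

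- **Candidates:** "Predictor variables including age, gender, baseline pain, physical function, duration of symptoms, mood/anxiety, self-efficacy, co-morbidities and exercise adherence will be measured".
- **Structure:** "Analyses will be performed separately for MDT and IP group treatments".
- **Responses:** "change in HAGOS function in daily living score pre and post intervention", with a 5.2-point MCID in parentheses, and "numeric pain rating on the VAS".
- **Selection:** each candidate is screened in a univariate logistic model; "those associated with the outcomes will be entered into the multivariate logistic regression model"; variables with p above 0.05 are then removed. Odds ratios with 95% intervals are reported. The section makes no adjustment for multiple testing.

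Two other places bear on this. The section on randomisation and allocation concealment says that "the study will only recruit male participants", and Table 1 excludes women. The outcome section describes pain as marked on a "100 mm horizontal VAS anchored by the terms" for no pain and worst pain, a scale it regards as suitable for parametric analysis.

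**The concern.** Some of these rules conflict with each other or with the rest of the article. Logistic regression needs a binary response, but the pain response is a numeric rating and no responder threshold for it appears anywhere. Gender takes a single value in this trial. The HAGOS response is worded as a change around the intervention, which sits loosely beside the stated 12-week endpoint.

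The method is also weak for the data available. Cutting HAGOS change at 5.2 points discards information. Fitting each arm alone halves the sample, and screening followed by elimination keeps a predictor only when its estimate happens to be large. Odds ratios that survive such selection tend to be too far from 1. Exercise adherence, recorded during follow-up, is listed beside baseline characteristics as if it were the same kind of variable.

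At stake is the reliability of any list of predictors of recovery that the trial publishes. The trial means to inform practice, so such a list could be taken up by clinicians.

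**Working it through.** **1. Conflicts that need no arithmetic**

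- Gender is a listed candidate, but all participants are male. A constant column beside an intercept gives a matrix of rank 1, so no odds ratio for gender exists. Nine named candidates become eight usable ones.
- The model is named first as multiple regression and then as logistic regression. HAGOS change carries a cut; the VAS does not. The logistic model for pain therefore has no defined outcome.

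**2. Evaluable participants per arm**

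The article gives no events-per-predictor figure to reproduce. Its Sample size section gives 43 per group. That figure does not follow from its stated inputs: 2 × (1.96 + 0.84)² × 11² / 5.2² is about 70.2, so 71 per group. That is a separate matter. Here 43 is used because 50 randomised per arm less about 15% dropout gives 50 × 0.85 = 42.5.

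**3. Events per candidate predictor**

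Events are the smaller outcome class, n × min(r, 1 − r), where r is the responder share on HAGOS. The article gives no r, so it is assumed and varied. The result is divided by 8.

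| Per arm | Assumed r | Smaller class | Per candidate |
|---|---|---|---|
| 43 | 50% | 21.5 | 2.7 |
| 43 | 40% or 60% | 17.2 | 2.2 |
| 43 | 30% or 70% | 12.9 | 1.6 |
| 43 | 20% | 8.6 | 1.1 |
| 50 (no dropout) | 50% | 25.0 | 3.1 |

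A 50% share is the most favourable value; any other gives fewer events. The divisor is the number of candidates screened, because selection bias follows the candidates tried and not only those kept.

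**4. Chance of at least one false predictor**

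Assume that all eight candidates are null and independent.

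- By formula, per model: 1 − 0.95⁸ = 0.337.
- By formula, over the two HAGOS models (one per arm): 1 − 0.95¹⁶ = 0.560.
- By simulation of the screening and backward elimination, with n = 43, r of 50% or 30%, entry thresholds of 0.05 or 0.20 (the article states none) and 1,500 runs per setting: 0.273 to 0.311 per model.
- Over the two HAGOS models, from the simulated values: 1 − (1 − 0.273)² = 0.47 to 1 − (1 − 0.311)² = 0.53.

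The simulation falls a little below the formula. Together they span about 27–34% per model and 47–56% over the two HAGOS models.

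**The case against.** The best defence is that this is a secondary analysis, that the article openly states there is no multiplicity adjustment, and that the primary comparison does not depend on it. All of that is true and limits the weight of the point.

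The text can also be read as multiple regression for the numeric VAS and logistic regression for HAGOS response, leaving any cut-off to an analysis plan. The logistic sentence refers to outcomes in the plural, which tells against this reading. Even if it is right, the text does not say so. A conflict between the stated model and the stated response is more than an omitted detail.

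Several stronger readings are tempting but not supported:

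- **That the whole analysis cannot be run.** Gender simply drops out, and the HAGOS logistic model can then be fitted. Only the pain model is undefined.
- **That there are two competing time points.** The same paragraph fixes 12 weeks, in line with the study aims, Table 4 and the Sample size section. The wording of the HAGOS response is loose, but it does not set a second endpoint.
- **That the authors plan to claim different predictors in each arm.** Neither the hypotheses nor the analysis section proposes such a claim. Separate models merely invite it.
- **That the false-predictor risk is 81%** (1 − 0.95³²). This counts two logistic models for VAS, which the text does not define.

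A reader may add that pooled interaction tests bring their own multiplicity: eight predictors on two outcomes is 16 tests, again 56% by the same formula, with low power in about 86 participants. That stands, and the fix below is limited accordingly. Relating adherence to outcome is also legitimate if it is not read causally.

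**Conclusion.** The point holds as a defect of specification and method in a secondary analysis. Two faults follow from the text alone: the pain model is undefined as a logistic regression, and gender cannot be estimated. The third is one of size. At the planned 15% dropout there are at most about 2.7 events per usable candidate, falling to 1.1 at a 20% responder share; full retention would raise the maximum only to 3.1.

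If every candidate were null, a false predictor would appear in roughly 27–34% of models and in 47–56% of pairs of HAGOS models. Spurious predictors and inflated odds ratios are likely, not certain. These figures rest on an assumed responder share and on independent null predictors. Pain, function and mood are plausibly correlated, which would change the exact percentages but would not add events. The primary comparison is not touched, so the change is advisable but not critical to the trial's main conclusion.

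**What to change.** Rewrite the paragraph as follows:

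- For each outcome (HAGOS function in daily living, VAS pain), fit one linear model to the continuous 12-week score with both arms pooled. Include treatment, the baseline value of that outcome (entered once, since baseline pain and function are already listed) and a short prespecified set of baseline predictors.
- Remove gender, univariate screening and elimination by p-value.
- State 12 weeks as the only time point.
- Report adherence separately, as an association with a post-randomisation variable.
- Label the analysis exploratory and report estimates with confidence intervals.
- If any difference in a predictor between arms is to be claimed, base it on a treatment-by-predictor interaction, reported as exploratory and low-powered.

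The cost is a change of wording, with no new data. The article already provides for documented and justified changes to the analysis plan. The loss is that odds ratios for a response above 5.2 points give way to mean differences; a descriptive responder table can be kept for readers who want it.

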**Methods/design:**

The trial will be conducted at the Defence Medical Rehabilitation Centre, Headley Court, UK. One hundred military male participants with clinical indicators of non-arthritic intra-articular hip pain will be randomly allocated to either: (1) 7-day residential multidisciplinary team intervention, *n* = 50; (2) 6-week physiotherapist-led outpatient intervention (conventional care), *n* = 50. Measurements will be taken at baseline, post-treatment (1-week MDT group; 6-weeks physiotherapy group), and 12-weeks. The primary outcome measures are the function in daily living sub-scale of the Copenhagen Hip and Groin Outcome Score (HAGOS), the physical function subscale of the Non-arthritic Hip Score (NAHS), and VAS pain scale. Secondary outcomes include objective measures of physical capacity and general health. An intention-to-treat analysis will be performed using linear and mixed models.

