### Primary hypothesis

No studies have compared the effects of MDT residential rehabilitation interventions versus conventional outpatient care for non-arthritic hip pain. However, systematic reviews and RCT’s provide evidence that MDT inpatient rehabilitation programmes are more effective than usual care (moderate evidence) to improve pain, well-being and self-reported function in heterogeneous patient groups with musculoskeletal conditions [17–20]. Therefore, we will test the following primary hypothesis:i.A 7-day multidisciplinary residential intervention will result in greater improvements in treatment outcomes compared to individualised outpatient treatment in young adults with non-arthritic hip pain.

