### Outcome measures

Outcome measures with proven validity and reliability have been selected based on those recommended for clinical trials of intra-articular FAI [53], and current practice in UK military rehabilitation [54]. Standardised instruments recommended by OMERACT-OARSI guidelines [55] will also be included. These guidelines require measures of pain, physical function and a global assessment of health related quality of life. Participants will be assessed at baseline, on completion of treatment (1-week MDT group; 6-weeks IP group) and 12-weeks follow up (Fig. 1). The follow-up time-frames are the same for both groups (12-weeks), and all participants will be assessed at baseline and 12-weeks on the same clinical outcome measures. The inclusion of post-treatment measures may help reveal if any differences occur as a consequence of the different interventions (e.g., the immediate post-treatment scores by group). All outcome measures will be conducted, administered and overseen by the same supervising therapist on each occasion. Outcome measures used in the study are summarised in Table 4.

**Table 4 Tab4:** Summary of outcome measures

Primary outcome measure^a^	Data collection instrument
Function in daily living	Subscale of HAGOS
Physical function, activity level	Subscale of HAGOS
Hip symptoms, numeric pain rating	Subscale of HAGOS, subscale of NAHS, VAS
Secondary outcome measures^a^	
General health status	EuroQol -5D (EQ-5D-3 L)
Mood, anxiety, depression	HADS
Objective functional performance	6-minute walk test
Hip range of motion	Clinical methods and goniometry
Dynamic balance/postural control	Modified Star Excursion (Y-Balance) Test
Hip muscle strength	Hand held dynamometry
Treatment efficacy & self efficacy	SIRBS
Adherence to home-based exercise	Training Diary and 11-point rating scale
Patient demographics & past treatment	Questionnaire

^a^The primary end-point for data analysis is 3-months. All measures will be taken at baseline, post-treatment (1-week MDT group; 6-weeks IP group), 3-months with the exception of patient demographics which will only be assessed at baseline

*HAGOS* Copenhagen Hip and Groin Outcome Score, *NAHS* non-arthritic hip score, *VAS* visual analogue scale, *HADS* hospital anxiety and depression scale, *SIRBS* sports injury rehabilitation beliefs survey

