### Sample size

The primary endpoint will be change from baseline to 12-weeks in (a) the HAGOS ‘physical function in daily living’ subscale and (b) VAS numeric pain rating. Sample size calculation is based on clinically relevant changes over the study period (e.g., score changes between baseline and follow-up should be, on average, subjectively perceptible by the participant). The minimum clinically important difference (MCID) in the HAGOS subscale has been suggested to be 4.8–5.2 points [53]. Between participant standard deviations have not been widely reported for the VAS using intra-articular hip pain patients [1, 10]. Therefore, the required sample using a MCID of 5.2 between groups on the HAGOS subscale and a standard deviation of 11 points, with a significance level of 0.05 (2 tailed) and a power of 80 %, is 43 per group. Allowing for an estimated drop out rate of approximately 15 % at the 12-week follow-up, a total of 100 participants will be recruited into the study. Based on current referral rates it is anticipated this sample target will be met from routine referrals to DMRC Headley Court and no additional strategies to promote enrolment are required. The sample size was calculated using G*Power software Version 3.0.10 (Franz Faul, Universitaet Kiel, Germany). There is currently no RCT reporting the effects of a residential MDT intervention versus outpatient individualised treatment approaching this sample size in the available literature.

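### The primary outcome set differs between sections, no success rule is stated and multiplicity adjustment is ruled out, so 5% for the primary hypothesis is not guaranteed

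*Protocol article*

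**What the plan says.** The protocol article describes the primary outcome in several places.

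- **Abstract, Methods/design:** three measures. "The primary outcome measures are the function in daily living sub-scale of the Copenhagen Hip and Groin Outcome Score (HAGOS"), followed by "the physical function subscale of the Non-arthritic Hip Score (NAHS), and VAS pain scale".
- **Outcome measures, Table 4:** three primary rows. The first is HAGOS daily living. The second, "Physical function, activity level", is another HAGOS subscale. The third covers hip symptoms and pain and lists "Subscale of HAGOS, subscale of NAHS, VAS". Together the rows hold five scores.
- **Descriptive data (list of primary instruments):** the HAGOS with six domains, the NAHS with four domains and the VAS, with no subscale selected. The NAHS is there given the task of checking whether its results resemble those of the other self-report measures.
- **Sample size:** two measures, "change from baseline to 12-weeks in (a) the HAGOS ‘physical function in daily living’ subscale and (b) VAS numeric pain rating".

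The Primary hypothesis names no outcome. It says that the residential programme "will result in greater improvements in treatment outcomes compared to individualised outpatient treatment". The primary aim, under Study aims and hypothesis, is pain and physical function.

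On error control, the Statistical analysis section states "No statistical adjustment will be made for multiple testing" and sets every test two-sided at 5%. Tukey's procedure is planned only for post-hoc comparisons after a significant result. The primary time point of 12 weeks is the same throughout.

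**The concern.** A confirmatory trial needs one stated set of primary outcomes and a rule that turns their results into success or failure. This article has differing sets and no rule. The NAHS shows the problem most clearly: it is a function primary in the Abstract, a symptom and pain primary in Table 4, a comparison measure in the outcome descriptions, and absent from the Sample size section.

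Because adjustment is expressly ruled out, the error rate of the primary claim depends entirely on the missing rule. Under one rule the claim is held at 5% or below. Under another, two to five unadjusted tests could each support a statement that the residential programme is superior. Participants and assessors are unblinded and all the candidate measures are self-reported, so clear pre-specification carries more weight than usual.

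**Working it through.** **Inputs from the document.** Alpha is 0.05 two-sided per test, with no adjustment (Statistical analysis). The number of primary measures, k, is 2 (Sample size), 3 (Abstract) or 5 (Table 4, if every listed score is tested). The article gives no correlation between outcomes, so the correlations below are assumptions. The article states no familywise error rate that could be reproduced.

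**If any one significant primary counts, independent tests.** P(at least one false positive) = 1 − 0.95^k:

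- k = 2: 1 − 0.9025 = 9.8%
- k = 3: 1 − 0.8574 = 14.3%
- k = 5: 1 − 0.7738 = 22.6%

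**The same rule with correlated tests.** These figures come from simulating equicorrelated normal test statistics, 1,000,000 draws per cell:

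| Assumed correlation | k = 2 | k = 3 | k = 5 |
|---|---|---|---|
| 0.3 | 9.5% | 13.6% | 20.9% |
| 0.5 | 9.1% | 12.5% | 18.3% |
| 0.7 | 8.3% | 11.0% | 14.9% |
| 0.8 | 7.8% | 9.8% | 12.7% |

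**Counting only false results that favour the residential arm.** For independent tests the rate is 1 − 0.975^k, which gives 4.9%, 7.3% and 11.9%. At correlation 0.8 the simulation gives 3.9%, 4.9% and 6.4%. The reference value for these is 2.5%, because a two-sided 5% test places half its error in each direction.

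**If all primaries must be significant.** The chance of a false claim cannot exceed that of any single test, so it is at most 5% and no adjustment is needed.

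**What the sample-size calculation covers.** Only HAGOS daily living has one. Its stated inputs are a difference of 5.2, SD 11, 80% power and two-sided 5%. They give n = 2 × (1.960 + 0.842)² × (11/5.2)² = 70.3, so 71 per group by the normal approximation, against the stated 43. At 43 per group, power is 58–59%. This is a separate defect. It matters here because HAGOS daily living can be described as the only measure with a sample-size calculation, but not as a measure shown to be adequately powered.

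**Cost of keeping an any-one rule with Bonferroni.** With the same inputs, 80% power per outcome needs 86 per group at 0.05/2, 94 at 0.05/3 and 105 at 0.05/5, before dropout.

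**The case against.** The best defence is that the article points to one pair. The primary aim is pain and physical function, the Sample size section defines a single endpoint as (a) HAGOS daily living and (b) VAS, and the predictor analysis uses the same two as response variables. Both also appear in the Abstract and in Table 4. If the joining word in the Sample size section means that both are required, 5% each causes no inflation. That reading is reasonable, but it is not stated, and it does not explain why the Abstract and Table 4 list other primaries.

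Several stronger readings are tempting and are not supported:

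- **That the 5% level fails.** This assumes an any-one rule that the article never states.
- **That the list is free to be picked after the data are seen.** The article requires changes to the analysis plan to be documented and justified, and its registration date precedes planned recruitment. The registry record is not at hand and may fix a list. What stands is that choosing among lists already in the article would not obviously count as a change.
- **That there are definitely five primary tests.** Table 4 sets outcomes against instruments and does not specify tests, so five is the upper reading of that table.
- **That the NAHS subscale in the Abstract does not exist.** None of the four NAHS domains bears that name, but it may be a loose label for the physical activities domain.
- **That the post-treatment comparison adds to the primary error rate.** The primary time point is fixed at 12 weeks.

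A separate analysis plan may exist and could settle the rule. It would not remove the conflict between sections of this article.

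**Conclusion.** The inconsistency is certain and visible in the text: the sections give different primary sets, and the NAHS has incompatible roles. It is equally clear that no success rule is given and that adjustment is ruled out. The consequence is that the error rate of the primary claim is not guaranteed to be 5%. It does not follow that it exceeds 5%.

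The size is conditional. Under an any-one rule the two-directional rate runs from 7.8% (two measures, assumed correlation 0.8) to 22.6% (five measures, independent), and about half of that if only results favouring the residential arm count. Under an all-required rule there is no inflation. This needs correction before analysis, because the confirmatory claim is at present undefined.

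**What to change.** State one identical primary set at 12 weeks in the Abstract, the Primary hypothesis, Table 4, the list of primary instruments and the Sample size section, and add an explicit success rule that holds 5%. Two choices are acceptable:

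1. HAGOS daily living alone. It is in every explicit list and is the only measure with a sample-size calculation. VAS is tested at 5% only if HAGOS daily living is significant.
2. HAGOS daily living and VAS as co-primaries, with both required at 5%. This fits the stated aim and the wording of the Sample size section.

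In either case, make the NAHS and the other HAGOS subscales secondary, reported as estimates with 95% confidence intervals and no confirmatory claim.

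The cost is wording only, with no change to data collection, and the NAHS loses primary status. Choice 2 also lowers power. As an illustration, if each outcome had 80% power, joint power would lie between 0.8 × 0.8 = 64% (independent) and 80% (perfectly correlated). The article gives no effect size or SD for the VAS, so the actual loss cannot be computed from it.
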